### Recruitment

Recruitment will occur via newsletters and posters at community organizations and health centers in Halifax, Nova Scotia. Furthermore, staff at the local HIV Clinic have agreed to approach eligible individuals and provide them with a study information brochure. To obtain a sample that is diverse in terms of ethnicity, gender, and severity of HIV disease, we will also employ snowball sampling techniques, whereby potential participants will be asked to identify other potential participants. All interested individuals will contact the study coordinator. The coordinator will explain the general purpose and procedures of the study, risks and potential benefits, time commitment, and responsibilities of the participants. Each potential participant will be informed that health care services will not be affected by study participation or withdrawal. A copy of the consent form will be provided and reviewed, and all the questions will be answered to the potential participant’s satisfaction. Potential participants who remain interested in enrolling in the study will be asked to sign the consent form approved by the local Research Ethics Board (REB).

### Randomization

After baseline assessment, an individual not directly involved in the study will randomly assign participants in a 1:1 ratio to the yoga or control group using a random computer generator. Group assignment of each participant will be concealed in individual opaque envelopes that will remain sealed until after completion of the baseline assessment. The number of participants screened and randomized to each group will be recorded, as per the CONSORT extension for randomized pilot trials [81].

### Ethical Considerations

The study protocol was approved by the REB (protocol reference #1022158). The procedures will be followed in accordance with institutional ethical standards and the Helsinki Declaration. The trial was registered on ClinicalTrials.gov. Proposed amendments to the protocol will be submitted for review to the REB. For ethical reasons, we cannot ask participants to avoid making medication changes; any changes participants make to their medications will be documented. Unanticipated or adverse events will be reported immediately to the REB. Participant confidentiality and autonomy will be maintained throughout the study, and data will be anonymized and secured. Study data will be stored in a locked office at Dalhousie University. Electronic data will be stored in encrypted form and will exclusively be accessed by the research team. Restricting access to data on-site until the data have been appropriately coded and deidentified will mitigate the risk of residual disclosure. All data will be destroyed after 7 years. Decisions to stop participating will be respected. To offset participants’ personal and travel costs, we will provide bus tickets for assessments and yoga sessions, and we will provide parking reimbursement, snacks, and honoraria for the assessments.

### Intervention Protocols

#### Yoga Group

Groups of 4 to 5 participants will engage in 60-min group-based Hatha-style yoga sessions 3 times per week for 12 weeks under the supervision of a yoga-certified physiotherapist at a local yoga studio. Classes will begin with a 15-min warm-up, which includes seated meditation, breathing exercises, shoulder and neck stretches, back mobility exercises, and sun salutations. Then, participants will perform 10 min of standing and 15 min of balance poses, followed by 10 min of abdominal work and back-bends. The class will finish with 5 min of final rest (savasana). The yoga protocol can be seen in Table 1.

**Table 1 table1:** Yoga protocol.

Warm-up (15 min)	Standing poses (10 min)	Balance poses (15 min)	Abdominals and back bends (10 min)	Cool down (10 min)
Seated meditation; alternate nostril breathing; bellows breath; shoulder/neck stretches; cat-cow forward fold; sun salutations	Warrior 1; warrior 2; triangle; extended side angle; reverse warrior; high lunge with twist	Tree pose; eagle pose; standing holding knee; modified warrior 3 (chair support); half moon	Bird-dog; side plank; bridge; cobra; sphinx	Twist; cobbler’s pose; hip stretches; corpse pose; side-lying; seated om

#### Yoga Protocol

Yoga mats, blocks, chairs, and straps will be provided to the participants. Postures will be modified for people with balance impairments or neuropathies. If participants are unable to get down to the floor or balance without support, postures will be performed with the use of a chair or other props. As Indigenous people are overrepresented in the HIV epidemic in Canada (they represented 11.3% of all new infections in 2016) [84], the sample population should reflect the cultural diversity within the catchment area of the study. Every month, a smudging ceremony with an Elder representing the Indigenous people will take place for 5 to 10 min before class commencement. The rationale for performing the smudging ceremony is that it is commonly associated with yoga practices [85]; in fact, a recent survey of 360 yoga practitioners identified spirituality as a common reason for starting and maintaining their yoga practice [86].

#### Attendance Policy

Of the total of 36 sessions (3 classes a week for 12 weeks), each participant will be encouraged to attend 70% of classes. Consideration will be given to withdrawing a participant from the study if the participant cancels or does not attend more than 6 sessions for reasons other than illness. In the event of a reversible illness that results in the participant being absent for more than 6 sessions, the participant will be withdrawn from the study and offered to be reenrolled in the yoga group after an 8-week washout period. If a session is cancelled, a make-up session will be scheduled.

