#### Control Group

The control group will be asked to continue with its regular exercise routine, and the group will be asked to not make any changes during the study. Interested participants in the control group will be offered the opportunity to attend ongoing yoga classes as frequently as they would like, following study completion.

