#### Assessment Protocol

As per the CONSORT extension for pilot RCTs, the number of participants screened for eligibility, randomly assigned, received intended treatment, and assessed for each objective will be recorded [81]. Study data will be collected in the Physiotherapy department at Dalhousie University and managed using Research Electronic Data Capture (REDCap) software (REDCap Inc) [87]. The authors will provide access to the study’s REDCap (REDCap Inc) data upon request. Table 2 outlines the outcome variables and measurement tools.

**Table 2 table2:** Outcomes and measurement tools.

Outcome	Measurement tool	Objective measure or self-report
Yoga readiness (previous experience with yoga, injuries and ability level)	Yoga readiness questionnaire (yoga group only)	Self-report
Cognitive performance	Communicating Cognitive Concerns questionnaire; Brief Cognitive Ability Measure	Self-report; objective
Motor function (balance, walking speed)	Community Mobility and Balance Scale; 10-meter walk test	Objective; objective
Mental health	Hospital Anxiety and Depression Scale	Self-report
Quality of life	Medical Outcomes Survey	Self-report
Medication adherence	Simplified Medication Adherence Questionnaire	Self-report
Physical activity	Rapid Assessment of Physical Activity; Fitbit Flex 2—total distance walked (km) and steps taken per day	Self-report; objective
Participant satisfaction, safety, comfort, fatigue, and benefits	Postparticipation survey (yoga group only)	Self-report

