##### Primary Measures

Many domains of feasibility will be assessed by both participants and study personnel using monitoring processes and a 13-item paper-based post-intervention questionnaire, which includes both questions on a Likert scale ranging from strongly disagree to strongly agree and open-ended questions (see Multimedia Appendix 1):

Project coordination (team building, communication and meetings, collaboration, consensus building, troubleshooting, scheduling, protocol consistency, and timelines). Any issues with (or changes to) the study protocol or scheduling will be documented.Participant issues (recruitment, comfort, satisfaction, safety, attendance, time commitment, attrition, and reasons for ineligibility drop out/declining to participate), as assessed by the postintervention questionnaire and documentation by the study coordinator.Assessment protocol elements (time and personnel requirements, usefulness of outcome variables, participant burden, and feasibility) will be recorded by the study coordinator.Intervention protocols (time, equipment, and personnel requirements) will be recorded by the study coordinator.Data quality (completeness, intra/interparticipant variability, interpretability, and trends) will be checked by the study coordinator. Per the CONSORT checklist, our a priori adherence and satisfaction criteria will be met if participants attend 70% of the yoga sessions and if 70% of the participants are satisfied with the yoga intervention as per the postparticipation questionnaire.

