##### Secondary and Tertiary Measures

Cognition, physical performance (balance, walking speed), physical activity, and affective (mental health, quality of life, and medication adherence) evaluations will be administered at baseline and postintervention (12 weeks) by a trained assessor, blinded to the group assignment. The rationale for blinding the assessor is to reduce bias in scoring during the assessment sessions. The estimated length of time for the assessment sessions is 2 hours per participant. We will measure *cognitive function* using the Brief Cognitive Ability Measure (B-CAM), a computerized cognitive test developed for PLWH, using Rasch measurement theory and analysis that takes 30 min to administer [88,89]. The B-CAM provides a measure of global cognition that is calibrated—the intervals between logits are equal, meaning the data are continuous [88,90].

Cognitive domains tested with the B-CAM include visual detection (reaction time), Flanker task (response inhibition) [91], memory (learning and recall of 8 words), Shape 2-back (working memory) [92], Corsi block-tapping forward and back tests (visuospatial memory) [93], verbal fluency (letters F-A-S in English) mini Trail Making Test B (executive function) [94], and the Tower of London test (planning) [95]. The scoring of the B-CAM ranges from 0 to 24, with higher values indicating better global cognition [90]. To reduce the likelihood of practice effects, different versions of the B-CAM are performed at baseline and final assessments [90]. Group-based trajectory analysis has revealed that no practice effects were found at the item level [90].

Self-reported cognition will also be assessed using the C3Q, an 18-item paper-based questionnaire that was developed to estimate the presence and frequency of memory, attention, executive function, visuospatial, speech and language, behavior and emotion, and cognitive challenges among PLWH [82]. The frequency of such challenges are recorded by the participant on a 3-point scale: frequently (almost every day), sometimes (once a week), or rarely (once a month) [82].

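### The attendance policy withdraws yoga participants from the study, not just from classes, which puts the 12-week data needed for the intention-to-treat analysis at risk in one arm only

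*Protocol article*

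**What the plan says.** The Attendance Policy (Protocol article, Intervention Protocols) sets 36 sessions, 3 a week for 12 weeks, and says that "each participant will be encouraged to attend 70% of classes". Two clauses then deal with absence:

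- **Absence for reasons other than illness (discretionary):** "Consideration will be given to withdrawing a participant from the study if the participant cancels or does not attend more than 6 sessions".
- **More than 6 sessions missed through a reversible illness (mandatory):** "the participant will be withdrawn from the study and offered to be reenrolled in the yoga group after an 8-week washout period".

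The policy adds: "If a session is cancelled, a make-up session will be scheduled".

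For the comparator, the Control Group section says: "The control group will be asked to continue with its regular exercise routine". Controls have no sessions to attend.

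Under Secondary and Tertiary Measures, the cognitive, physical and affective "evaluations will be administered at baseline and postintervention (12 weeks) by a trained assessor, blinded to the group assignment". Under Primary Measures, "our a priori adherence and satisfaction criteria will be met if participants attend 70% of the yoga sessions". The Data Analysis section plans both intention-to-treat and per-protocol analyses of the secondary variables, and intends the results to feed later sample size calculations. The Assessment Protocol says that the numbers "randomly assigned, received intended treatment, and assessed for each objective will be recorded".

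**The concern.** Stopping an intervention and leaving a trial are different events. An intention-to-treat analysis needs outcomes from everyone randomised, including those who stopped attending. Here poor attendance leads to leaving the study. Nothing in the article keeps a withdrawn person in follow-up.

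Three features make this worse than ordinary dropout:

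- **It is one-sided.** A control with the same illness stays in and is assessed at 12 weeks. A yoga participant is withdrawn and offered a second course after recovery.
- **It is plausibly informative.** Illness and low engagement are likely to be related to cognition, mood, balance and quality of life.
- **It cannot be repaired later.** No analysis plan can recover a 12-week assessment that was never done.

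The primary feasibility results are exposed too. The rule itself creates attrition. It can raise the adherence figure if withdrawn people leave the denominator, or lower it if they stay in and their remaining sessions count as missed.

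**Working it through.** **Plan's own figure.** 3 × 12 = 36 sessions, as stated.

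**Threshold against target.** 0.70 × 36 = 25.2, so 26 sessions are needed (25/36 = 69.4%; 26/36 = 72.2%). That allows 10 absences, but the rule acts at 7, which is attendance of at most 29/36 = 80.6%. Someone who misses 7 to 10 sessions therefore meets the 70% criterion, yet may be withdrawn, and must be if 7 or more of those absences come from a reversible illness. At 3 classes a week, 7 sessions last 7/3 ≈ 2.3 weeks.

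**How often the rule would act.** The documents give one attendance figure, 89%, from a cited study of yoga and meditation (Anticipated Challenges and Limitations). They give no illness rate. The assumptions are:

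- mean attendance 89% or 80%;
- 25% or 50% of absences due to illness;
- separate counts for the two clauses, both always applied (an upper bound for the discretionary one);
- no make-up sessions;
- absences either independent, or with within-person correlation 0.2 (beta-binomial).

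Exact check for independent absences: P(more than 6 of 36) for one count is the upper tail of Bin(36, p), where p is the absence rate times that cause's share.

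- 89%, 25% illness: other p = 0.11 × 0.75 = 0.0825, tail 0.0258; illness p = 0.0275, tail 0.00005.
- 89%, 50% illness: p = 0.055 for each cause, tail 0.0031 each.
- 80%, 25% illness: other p = 0.15, tail 0.290; illness p = 0.05, tail 0.0018.
- 80%, 50% illness: p = 0.10 for each cause, tail 0.0628 each.

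Simulation of 400,000 participants per scenario. The last two columns give mean adherence if triggered participants are dropped, or kept with later sessions counted as missed. Without the rule it equals the assumed attendance.

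| Attendance | Correlation | Illness share | Trigger | Of these, would have reached 26 | Dropped | Kept |
|---|---|---|---|---|---|---|
| 89% | 0 | 25% | 2.6% | 96% | 89.3% | 88.7% |
| 89% | 0 | 50% | 0.6% | 88% | 89.1% | 88.9% |
| 89% | 0.2 | 25% | 16.1% | 28% | 94.3% | 85.8% |
| 89% | 0.2 | 50% | 12.0% | 12% | 93.4% | 87.1% |
| 80% | 0 | 25% | 29.2% | 72% | 82.8% | 75.6% |
| 80% | 0 | 50% | 12.4% | 50% | 81.4% | 78.5% |
| 80% | 0.2 | 25% | 33.5% | 22% | 91.0% | 73.2% |
| 80% | 0.2 | 50% | 26.7% | 9% | 89.4% | 75.6% |

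With about 12 people in the yoga arm (25/2), the expected number triggering runs from 12 × 0.006 = 0.07 to 12 × 0.335 = 4.0. The median trigger falls between week 7.3 and week 11.0, before the 12-week assessment.

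**Mandatory illness clause alone** (25% to 50% illness share):

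- 89%: 0.005% to 0.3% independent; 1.3% to 8.3% with correlation 0.2.
- 80%: 0.2% to 6.3% independent; 3.7% to 19.4% with correlation 0.2.

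**One illness covering exactly 7 sessions.** The person still meets 70% with at most 3 absences in the other 29. That probability is 0.945 if 5% of those are missed and 0.602 if 11% are missed. So most people withdrawn under the mandatory clause after one such illness would have been adherent by the protocol's own criterion.

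**Make-up sessions.** If half of all absences were made up, trigger rates at 80% attendance fall to 0.4% to 1.6% (independent) or 7% to 11% (correlation 0.2).

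**Precision.** Apart from bias, losing 2, 4 or 6 of 12 from one arm multiplies the standard error of the difference by √[(1/12 + 1/n)/(2/12)] with n = 10, 8 or 6, giving 1.05, 1.12 and 1.22.

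**The case against.** The strongest reply is that the loss of follow-up is inferred. The policy sits under the intervention protocols and does not say that the 12-week assessment is cancelled. A journal article may leave that to the full protocol, and planning both intention-to-treat and per-protocol analyses makes most sense if poor attenders' data are kept. That is a fair reason to call this a risk, not a certainty. It does not remove the point, because the benign reading needs the policy to mean leaving classes where it says leaving the study.

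Second, a returning participant was already randomised to yoga, so nobody crosses over and a second randomisation would be wrong. This is correct. What remains is that a fresh course after recovery exists in one arm only, with no statement of which baseline and which 12-week record would count.

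Third, the non-illness clause is discretionary, the mandatory clause is rare at 89% attendance (an expected 0 to 1 of 12), and the larger figures rest on assumptions outside the documents. All of this stands and limits the size claimed.

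Fourth, losses will be counted and reported, intention-to-treat covers only secondary variables, and the pilot disclaims conclusions on effect. Counting losses makes them visible but does not restore the data. The limited aims lower the stakes, though attendance and attrition are themselves among the primary feasibility measures.

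**Conclusion.** The concern holds. As written, the policy can remove randomised participants from the yoga arm only, in one case compulsorily, before the sole follow-up assessment. It also acts on people who could still meet the adherence criterion. The threshold conflict (7 absences against 10) is plain arithmetic. The missing 12-week data are conditional on withdrawal from the study meaning what it says.

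The size is uncertain: negligible at 89% attendance with independent absences, about 1 to 2 of 12 at 89% with correlation 0.2, and up to about 4 of 12 at 80%. These counts assume the discretionary clause is always used and no session is made up. The harm is to the feasibility description and to the preliminary data for a later trial, not to any proof of efficacy. It should be fixed because the change is cheap; confidence is medium.

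**What to change.** Reword the Attendance Policy so that absence leads, at most, to stopping classes. Then state that:

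- everyone randomised is invited to the 12-week assessment, and all yoga participants to the postparticipation survey, unless consent is withdrawn;
- participants absent through illness are analysed as randomised, on their original baseline and original 12-week date;
- any re-enrolled yoga course starts after that assessment and stays outside the main analysis;
- adherence is sessions attended out of 36, with make-ups counted as attended, for everyone randomised to yoga.

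Raising the class-stopping threshold to more than 10 absences would remove the conflict with the 70% criterion, but that is a matter of preference once follow-up is secured.

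The cost is a wording change, an ethics board amendment, and about 2 hours of assessment for each non-attender who agrees to return (roughly 0 to 4 of 12 under the assumptions above). The downsides are that the adherence figure may look less favourable than one based on completers only, and that classes of 4 to 5 may have to carry irregular attenders.

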## Results

### Data Analysis

All questionnaires and measures will be assessed for missing data. The data will be analyzed to determine if the assumptions for parametric tests are met. Descriptive statistics will be used to characterize the participants. As per the CONSORT extension for pilot studies, means of all outcomes, mean change, and 95% CIs will be calculated for each group separately. We will also follow the Sex and Gender Equity in Research guidelines [108] by disaggregating data by sex and gender. Participant dropouts will also be reported disaggregated by sex.

Independent *t* tests and Fisher exact tests will be used to compare the 2 groups at baseline. If the 2 groups differ at baseline, that variable will be included in the analysis as a covariate. We will analyze quantitative postintervention questionnaire responses using Chi-square tests, and open-ended responses will be analyzed thematically. Intention-to-treat and per-protocol analyses will be used in the analysis of the secondary variables. Changes in outcome variables will be examined between groups and within groups. Floor and ceiling effects will be calculated for the CB&M test. Effect sizes will be reported for each outcome. Alpha level will be set at .05, using 2-tailed for all inferences, and data will be analyzed with SPSS Version 25 (SPSS Inc). As this is a pilot study, sample size calculations are not recommended [81]. This pilot study will not be adequately powered to conclusively state the influence of the intervention on study outcomes, but if trends are promising, a future, more adequately powered trial will be planned. This pilot study will provide preliminary data for future sample size calculations.

Study enrollment began in January 2018, with results expected in October 2019.

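### Withdrawing yoga participants from the study after more than 6 illness absences, then offering re-entry straight into yoga, conflicts with intention-to-treat analysis and the 12-week assessment

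*Protocol article*

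**What the plan says.** Attendance Policy sets the schedule and the target: "Of the total of 36 sessions (3 classes a week for 12 weeks), each participant will be encouraged to attend 70% of classes". It then treats two kinds of absence differently.

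- For absence not due to illness, withdrawal is discretionary: "Consideration will be given to withdrawing a participant from the study if the participant cancels or does not attend more than 6 sessions".
- For illness, it is not. The condition is "In the event of a reversible illness that results in the participant being absent for more than 6 sessions", and the consequence is that "the participant will be withdrawn from the study and offered to be reenrolled in the yoga group after an 8-week washout period".

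Control Group has no matching provision: "The control group will be asked to continue with its regular exercise routine, and the group will be asked to not make any changes". Randomization describes one allocation, after baseline, in which an independent person will "randomly assign participants in a 1:1 ratio to the yoga or control group using a random computer generator". No second allocation is mentioned.

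Secondary and Tertiary Measures places the outcome assessments at baseline and at 12 weeks. Data Analysis states: "Intention-to-treat and per-protocol analyses will be used in the analysis of the secondary variables". It also plans comparisons of change between and within groups. Primary Measures makes feasibility primary, including attendance and attrition, with a criterion of 70% of yoga sessions attended.

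**The concern.** The rule selects on a health event that happens after randomisation, and it can act in one arm only. A yoga participant who is ill for long enough leaves the study and may come back recovered. The article gives no rule that would remove an equally ill control, who would on the ordinary reading be assessed at 12 weeks. Illness plausibly affects cognition, balance, mood, activity and quality of life, so with no true effect of yoga the selection would probably favour yoga.

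Three statements in the article pull against each other:

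- Intention-to-treat analysis needs outcomes on everyone randomised, but the rule takes people out of the study and not merely out of classes.
- Outcomes are due at 12 weeks, but a second course ends well after that.
- The adherence criterion tolerates more absences than the withdrawal rule does.

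Attendance and attrition are primary measures, so the feasibility results are exposed as well as the arm comparison. Those results, and the preliminary data for a later sample size calculation, are what the pilot is meant to supply.

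**Working it through.** **Inputs from the protocol article.** 3 classes a week for 12 weeks; withdrawal after more than 6 absences; 8-week washout; 70% attendance criterion; at most 25 participants allocated 1:1, so 12 or 13 per arm; outcomes at baseline and 12 weeks.

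**Assumed, because the article gives no figures.** The share q of each arm with a qualifying illness (10 to 20%) and the deficit d in 12-week change that it causes (0.3 to 1.0 SD).

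**1. The plan's own figure.** 3 × 12 = 36 sessions, which reproduces.

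**2. Withdrawal rule against adherence criterion.**
- 0.70 × 36 = 25.2, so 26 sessions meet the criterion and 36 − 26 = 10 absences are tolerated.
- The rule fires at the 7th absence, when up to 36 − 7 = 29 sessions remain attainable: 29/36 = 80.6%.
- Someone who attends the first 29 classes and is ill for the last 7 has met the criterion, yet is withdrawn just before the 12-week assessment.

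**3. Timing of a second course.**
- Seven consecutive absences take at least 7/3 = 2.3 weeks.
- Earliest end, counting the washout from withdrawal: 2.3 + 8 + 12 = 22.3 weeks after the start.
- If the 7th absence falls in week 12: 12 + 8 + 12 = 32 weeks.
- Controls are assessed at 12 weeks.

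**4. Chance that the rule is used at least once among 12 yoga participants.** 1 − (1 − q)^12 gives 72% at q = 10% and 93% at q = 20%.

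**5. Tilt in the comparison when yoga has no effect.** Ill controls stay in, so the control mean falls by q × d.
- If ill yoga courses are dropped, or replaced by illness-free second courses, the yoga mean does not fall and the tilt is q × d.
- If second courses carry the same illness risk, the tilt is q × d × (1 − q).

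| q | d (SD) | Dropped or illness-free second course | Same risk in second course |
|---|---|---|---|
| 10% | 0.3 | 0.03 | 0.03 |
| 10% | 1.0 | 0.10 | 0.09 |
| 20% | 0.3 | 0.06 | 0.05 |
| 20% | 1.0 | 0.20 | 0.16 |

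If every randomised person is assessed at 12 weeks and analysed once on the first course, both arms fall by q × d and the tilt is zero.

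**6. Feasibility figures, as an illustration.** Suppose 2 of 12 yoga participants are withdrawn for illness below 26 sessions and the other 10 meet the criterion. Counting everyone randomised gives 10/12 = 83% adherent. Leaving the two out gives 10/10, and counting successful second courses gives 12/12; both are 100%. Retention moves from 10/12 to 12/12 if completed second courses are counted.

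**The case against.** The strongest reply is that the article nowhere says second-course data are used. It commits to intention-to-treat for the secondary variables and fixes assessment at 12 weeks. The ordinary reading is analysis as randomised on first-course data, which avoids the tilt if those data exist. Which record is used for a restarted participant is also something an article may leave to a fuller analysis plan. This stands as far as it goes: a reader might infer that recovered second courses replace poor first ones, and the text does not support that. It does not rescue the withdrawal rule, which is stated outright. Leaving the study puts at risk the 12-week value that intention-to-treat needs, and dropping ill courses produces the same tilt as replacing them.

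Other stronger readings also fail:

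- **Automatic re-entry.** Re-entry is only offered, and it requires a reversible illness with more than 6 absences. The person was randomised to yoga; only the second entry is non-random.
- **A large bias.** Two of 12 people ill with a 1 SD deficit gives 2/12 = 0.17 SD, about half the pooled effect of 0.33 cited in the Introduction. But 1 SD is the top of the assumed range, and a reversible illness early in the course may have resolved by week 12.
- **Practice effects on the B-CAM.** Secondary and Tertiary Measures says alternate versions are used and reports no practice effects at item level. This does not settle a further administration, but it does not support a claim of contamination.
- **Inflated adherence and retention as fact.** Attendance, attrition and dropout reasons are to be recorded, so withdrawals should be visible. The risk lies in which of these enter the summary percentages.

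It is also fair that this is a pilot, which Data Analysis says cannot settle efficacy.

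**Conclusion.** The point holds as a conflict in the written rules. An illness-triggered withdrawal from the study that can occur only in the yoga arm does not fit the intention-to-treat analysis or the 12-week assessment, and it removes people who could still reach 81% attendance against a 70% criterion. Those statements rest on the article's own figures.

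The effect on results is conditional. If ill first courses are lost or replaced, the comparison probably tilts towards yoga by about 0.03 to 0.20 SD, for 10 to 20% ill and deficits of 0.3 to 1.0 SD. Both inputs are assumptions, and the direction depends on which course is analysed. For scale, the standard error of a difference with 12.5 per arm is √(2/12.5) = 0.40 SD, so the tilt is smaller than the sampling error. Pilot status lowers the weight of the efficacy comparison. It does not lower that of the adherence and retention figures, which are primary and which one or two people can move noticeably.

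**What to change.** Reconcile Attendance Policy with Primary Measures, Secondary and Tertiary Measures, and Data Analysis:

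1. State that missed sessions, for whatever reason, do not end study follow-up.
2. Seek the 12-week assessment from every randomised participant in both arms, whatever the attendance. Without this step, an instruction to use first-course data would leave the illness-selective loss in place.
3. Analyse each person once, in the arm randomised, on first-course outcomes and first-course attendance out of 36. Report any assessment not obtained as missing, by arm and with the reason.
4. Report any second course descriptively, outside all arm comparisons and outside the adherence, satisfaction and retention figures.

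Whether a participant may resume classes after illness is a clinical matter left to the investigators.

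The cost is a wording change, probably one or two extra assessment visits of about 2 hours each, and possibly one or two fewer favourable yoga records. Enrolment began in January 2018, so assessments already lost to the rule may not be recoverable; steps 3 and 4 can still be applied to those participants.
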